### Trial design

2.1

This prospective, randomized, triple-blind, placebo-controlled, multicenter clinical trial is designed to enroll 172 patients diagnosed with pGGNs. Participants will be randomly assigned in a 1:1 ratio to either the intervention group, receiving CJG, or the control group, receiving a placebo for CJG, utilizing stratified block randomization. Both cohorts will receive standardized health education and participate in a 3-month intervention with either CJG or a placebo, followed by a 1-year observational follow-up without the study drug. The study flowchart is depicted in Figure 1, while Figure 2 outlines the timeline for enrollment, intervention, and follow-up. The trial protocol is in compliance with the Consolidated Standards of Reporting Trials (CONSORT) guidelines for interventional studies.

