##### Short-term secondary outcomes

2.7.2.1

Psychological Status: Anxiety will be assessed utilizing the Beck Anxiety Inventory (BAI), with scores categorized as follows: 0–9 (minimal/no anxiety), 10–18 (mild anxiety), 19–29 (moderate anxiety), and 30–63 (severe anxiety) (17). Depression will be evaluated using the Beck Depression Inventory-II (BDI-II). Scores were classified as: 0–13 (minimal/no depression), 14–19 (mild depression), 20–28 (moderate depression), and 29–63 (severe depression) (18). Assessments will be performed at baseline and post-treatment.Quality of Life: Will be measured via the 36-item Short Form Health Survey (SF-36), a self-reported instrument assessing nine domains: physical functioning, role limitations due to physical health, bodily pain, general health perceptions, vitality, social functioning, role limitations due to emotional problems, mental health, and health change. Scores range from 0 to 100, with higher scores indicating better quality of life (19). Assessments will be performed at baseline and post-treatment.Medication Adherence: The adherence rate for CJG will be calculated using the formula: (Actual dose / Prescribed dose) × 100%. Patients will be categorized into three adherence groups: <80%, 80–120, and >120%. The count and percentage of cases in each group will be examined.

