### Sample size calculation

2.9

The primary outcome was the difference in changes in the maximum diameter of pGGNs before and after treatment. Based on preliminary pre-experimental results showing mean ± standard deviation (SD) differences of 1.11 ± 2.12 mm (intervention group) and 0.19 ± 1.25 mm (control group), sample size was determined using PASS software (version 2021). With a two-sided *α* = 0.05, 1-*β* = 0.90, 1:1 allocation ratio, and accounting for an anticipated 10% dropout rate, a minimum of 86 participants per group is required.

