### Statistical analysis

2.14

Data analysis will be conducted utilizing IBM SPSS Statistics version 28.0 (IBM Corp., Armonk, NY, United States). Efficacy analyses will encompass all patients who are randomly assigned (full analysis set, FAS; adhering to modified intention-to-treat principles) as well as all patients who completed the trial protocol (per-protocol set, PPS). Any discrepancies between the FAS and PPS analyses will be evaluated from both clinical and statistical standpoints. The safety analyses will be based on the safety set (SS), which includes all patients who received at least one dose of the investigational drug. All hypothesis tests will be two-tailed, with a significance threshold set at *α* = 0.05. *p*-values will be calculated from the relevant statistical tests, with *p* ≤ 0.05 being regarded as statistically significant.

To conduct a longitudinal comparison of the trajectories of changes in the maximum diameter of pGGN relative to baseline across various groups at follow-up time points, a linear mixed model will be utilized. This model will incorporate random subject intercepts to account for within-subject correlations arising from repeated measurements. The fixed effects will include group, follow-up time points, and their interaction, while covariates will consist of age and baseline pGGN maximum diameter. For other continuous variables, intergroup comparisons will be performed using independent samples t-tests for normally distributed data or Mann–Whitney U tests for non-normally distributed data, contingent upon the results of normality tests. Categorical variables will be compared using chi-square tests or Fisher’s exact tests. To assess the potential impact of distinct clinical characteristics on treatment efficacy, predefined subgroup analyses will be conducted, considering factors such as gender, age, smoking status, number of lung nodules, and risk stratification. Interaction tests will be performed to investigate whether differences in efficacy between groups vary across these subgroup factors.

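### Secondary continuous outcomes are compared by unadjusted tests picked by a normality test, so baselines the trial collects are not used as covariates

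*Protocol article*

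**What the plan says.** The Statistical analysis section gives the change in maximum diameter a linear mixed model with a random subject intercept and fixed effects for group, time and their interaction. In that model "covariates will consist of age and baseline pGGN maximum diameter". All other continuous variables are treated differently: "intergroup comparisons will be performed using independent samples t-tests for normally distributed data", or Mann–Whitney U tests otherwise, "contingent upon the results of normality tests". No covariate is named for them.

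Baselines exist for most of these outcomes. For BAI and BDI-II, and again for SF-36, the Short-term secondary outcomes section states: "Assessments will be performed at baseline and post-treatment". The Long-term secondary outcomes section schedules nodule density and Mayo risk at baseline, 3 months and 1 year. It defines the reduction rate as the fall in diameter divided by baseline diameter, at 3 months and 1 year.

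On allocation, the Trial design section says participants are assigned "utilizing stratified block randomization". The Randomization and blinding section repeats this with a fixed block size of four. Neither section names the stratification factors. Recruitment runs at three centres.

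**The concern.** The plan already accepts baseline adjustment for its primary outcome but sets it aside for the secondary ones. This is a stated choice of test, not a detail left open for an analysis plan. Three things follow.

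- **Precision.** A baseline that correlates with follow-up explains part of the outcome variance. An unadjusted two-sample test leaves that part in the error term.
- **Target of estimation.** A normality test on the trial data decides whether the result is a difference in means or a rank comparison. The answer could differ between outcomes, or between 3 months and 1 year for one outcome, so no single effect estimate with its interval is fixed in advance.
- **Repeated measures.** Density, Mayo risk and the reduction rate have two follow-up times but do not get the repeated-measures model used for diameter change.

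If a stratification factor is missing from a model, that analysis also ignores a design feature that normally reduces error variance. How much this matters depends on what the strata are.

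**Working it through.** **1. The plan's own sample size.** Inputs from Sample size calculation: mean changes 1.11 (SD 2.12) and 0.19 (SD 1.25) mm, two-sided α 0.05, power 90%, 1:1 allocation, 10% dropout.

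- Difference: 1.11 − 0.19 = 0.92 mm. Pooled SD: √((2.12² + 1.25²)/2) = 1.74.
- Normal approximation: 76 per arm, and 76/0.9 rounds up to 85.
- Unequal-variance t-test: 77 per arm (power 90.2%), and 77/0.9 rounds up to 86.

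The stated 86 per group reproduces. It rests on the primary outcome and does not depend on how secondary outcomes are analysed.

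**2. Gain from baseline adjustment.** Let ρ be the correlation between baseline and follow-up, with equal variances at both times. The document gives no ρ, so a range is assumed. Relative variances of the treatment comparison are:

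- follow-up value: 1
- change score: 2(1 − ρ)
- ANCOVA: 1 − ρ²

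The ratio of ANCOVA to follow-up value is therefore 1 − ρ². The ratio of ANCOVA to change score is (1 − ρ²)/(2(1 − ρ)) = (1 + ρ)/2.

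Power is Φ(0.45 × √(77/2)/√v − 1.96), where v is the relative variance, with 77 evaluable per arm. The standardised difference of 0.45 is assumed because it gives close to 80% power for the follow-up value.

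| ρ (assumed) | Variance cut vs follow-up value | Variance cut vs change | Power: follow-up value / change / ANCOVA |
|---|---|---|---|
| 0.3 | 9% | 35% | 79.7% / 65.5% / 83.3% |
| 0.5 | 25% | 25% | 79.7% / 79.7% / 89.7% |
| 0.6 | 36% | 20% | 79.7% / 87.7% / 93.7% |
| 0.7 | 49% | 15% | 79.7% / 95.0% / 97.4% |

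Confidence intervals narrow by 13%, 20% and 29% against follow-up values at ρ = 0.5, 0.6 and 0.7, and by 13%, 11% and 8% against change scores. Neither unadjusted option is best throughout: change scores do worse than follow-up values below ρ = 0.5 and better above it. ANCOVA is at least as precise as both, apart from one degree of freedom.

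**3. Mayo risk as an illustration.** Most inputs to the formula are fixed or nearly fixed within a patient, so ρ should be high. A simulation used the pilot diameter changes, 77 per arm and assumed patient mixes (age SD 6–12 years, smokers 10–40%, upper lobe 50–60%, diameter SD 2–3 mm, no spiculation or tumour history). Baseline correlation was about 0.93–0.95. Power was about 11–14% on follow-up values, 60–67% on change and 61–68% with ANCOVA. For this outcome the unstated choice between follow-up value and change matters far more than the step from change to ANCOVA.

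**4. Normality pretest.** In one skewed example (log-normal, 77 per arm, ρ = 0.6, 3,000 runs) the pretest chose Mann–Whitney every time. Type I error was 5.0–5.1% for the pretest procedure, the t-test and ANCOVA alike.

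**5. Strata, if the stratum is centre.** Simulation of an unadjusted t-test against a centre-adjusted model: three equal centres, blocks of four, 156 patients, standardised difference 0.45, 8,000 runs per setting. The centre share of variance is assumed.

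| Centre share | Power without / with centre | Type I error without centre |
|---|---|---|
| 0% | 79.1% / 79.2% | 4.9% |
| 5% | 79.6% / 81.2% | 4.4% |
| 10% | 81.4% / 83.9% | 3.9% |
| 20% | 82.6% / 87.9% | 2.5% |

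**The case against.** The strongest defence is that nothing here is invalid. Unadjusted tests are legitimate in a randomised trial, the outcomes are secondary, and the primary model already adjusts for baseline diameter. The reduction rate is also a function of the diameter measurement that the mixed model analyses at both times. All of that stands, and it limits the point to efficiency and interpretability.

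A reader might infer four stronger things that the document does not support.

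- **That baseline is ignored altogether.** The reduction rate contains baseline diameter by its formula, and the abstract lists changes in density as an outcome. Other tests may also be run on change scores. What is absent is baseline as a covariate.
- **That power rises from 80% to 90% or more for certain.** The larger gains assume that follow-up values are compared, which the article does not say. Against change scores the gain shrinks as the correlation rises.
- **That allocation was stratified by hospital and every model ignores the strata.** The factors are not named, and naming them may be left to the full protocol. If age or nodule size is a stratum, the primary model already includes it. The figures in step 5 come from an unadjusted t-test and do not carry over to the primary model.
- **That the pretest inflates type I error.** The one example run showed no inflation. The cost is an effect measure that depends on the data.

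**Conclusion.** The concern holds in limited form. The plan fixes unadjusted, pretest-selected tests for its secondary continuous outcomes while leaving baselines for BAI, BDI-II, SF-36, density and Mayo risk unused as covariates. The loss at ρ = 0.5 to 0.7 is 25% to 49% of the variance if follow-up values are compared, and 25% to 15% if change scores are. These correlations are assumptions, and the article does not settle which comparison applies. The reported effect measure is also left to the data.

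The strata point is secondary and conditional. If centre is a stratum and explains up to 10% of the variance (assumed), adding it gains under 3 power points in an otherwise unadjusted comparison, and leaving it out makes that test conservative. The primary model's baseline adjustment and the 86 per group stand unchanged.

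**What to change.** - Analyse BAI, BDI-II and SF-36 at month 3 by ANCOVA with the baseline value of the same measure as covariate.
- Analyse density and Mayo risk with a repeated-measures model like the primary one, adjusted for their own baseline. Do the same for the reduction rate, with baseline diameter as covariate.
- Drop the normality pretest. Report one adjusted mean difference with its confidence interval for each outcome, and keep a rank-based or bootstrap analysis as a sensitivity analysis.
- Name the stratification factors. If centre, or any other factor not already in the model, is a stratum, add it as a fixed effect to all models, including the primary one.

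The cost is a change of wording and slightly more analysis work, with no new data or patients. The article anticipated recruitment from September 2025; the change should be documented before unblinding.

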##### Long-term secondary outcomes

2.7.2.2

Reduction rate of the maximum nodule diameter: the reduction rate will be calculated as:

$$\frac{\left(\text{Bmax}-\text{Pmax}\right)}{\text{Bmax}}\times 100$$

Where: *Bmax* = baseline maximum diameter and *Pmax* = post-treatment maximum diameter.

Assessments will be performed at 3 months (treatment completion), and 1 year (follow-up completion). According to the *Guidelines for Clinical Research of New Traditional Chinese Medicine Drugs*: complete response (CR): complete resolution of the nodule on chest CT; partial response (PR): > 50% reduction in maximum diameter; stable disease (SD): 25–50% reduction in maximum diameter; progressive disease (PD): < 25% reduction or increase in maximum diameter (20).

Nodule density: In the CT lung window, the largest pGGN will be identified, and an experienced radiologist will measure the density in the central 60–80% of the slice showing the nodule’s largest area, avoiding vessels, bronchi, and pleura. The average of these three measurements will be calculated and recorded as the final density value for that time point. This evaluation will be performed at baseline, 3 months, and 1 year.Malignant risk of pulmonary nodules: Use the Mayo model formula: Probability = e^x^/(1 + e^x^), where e is approximately 2.718, and x = −6.8272 + (0.0391 × age) + (0.7917 × smoking history) + (1.3388 × tumor history) + (0.1274 × nodule diameter) + (1.0407 × spiculation) + (0.7838 × location) (21). Smoking, tumor history, spiculation, and upper lobe location are binary (1 if present, 0 if not), and nodule diameter is in mm. For multiple nodules, use the highest risk nodule. Assessments will occur at baseline, 3 months, and 1 year.

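### The four ordered response grades fall under a chi-square or Fisher rule that ignores their order; a rank or ordinal test would suit this secondary outcome better at no cost

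*Protocol article*

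**What the plan says.** Section 2.7.2.2 (Long-term secondary outcomes) names the reduction rate of the maximum nodule diameter, a percentage, as an outcome at 3 months and 1 year. Beneath it stands a four-grade classification. The upper grades are "complete response (CR): complete resolution of the nodule on chest CT; partial response (PR): > 50% reduction in maximum diameter". The lower grades are "stable disease (SD): 25–50% reduction in maximum diameter; progressive disease (PD): < 25% reduction or increase in maximum diameter". All four come from one quantity, and each step down means less shrinkage.

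Section 2.14 (Statistical analysis) gives one rule for categorical data: "Categorical variables will be compared using chi-square tests" or Fisher's exact test. The rank test appears in a separate sentence, for continuous data only: "For other continuous variables, intergroup comparisons will be performed using independent samples t-tests for normally distributed data or Mann–Whitney U tests". The article names no trend test, ordinal model or merging of grades for the response classification.

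**The concern.** Pearson's chi-square and Fisher's exact test ask whether the two arms differ in any way across the grades. If the four labels were shuffled, the p-value would stay the same. The clinical question is narrower: does CJG move patients toward better grades? An order-blind test answers that only indirectly, and with four occupied grades it spreads its power over three degrees of freedom. At stake are some power on a secondary classification and a p-value that does not match the question. The sample size and the primary mixed model are not involved.

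**Working it through.** **Inputs from the protocol.** Section 2.9 gives changes of 1.11 ± 2.12 mm (CJG) and 0.19 ± 1.25 mm (control), two-sided alpha 0.05, power 0.90, 1:1 allocation, 10% dropout and 86 per group. Section 2.7.2.2 gives the grade limits.

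**Assumed.** Changes are normal and every nodule has the same baseline diameter of 5, 6 or 8 mm. The protocol gives no baseline diameters.

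**Step 1: reproduce the stated sample size.** The difference is 1.11 − 0.19 = 0.92 mm. The normal approximation gives n = (1.960 + 1.282)² × (2.12² + 1.25²) / 0.92² = 10.51 × 6.057 / 0.8464 = 75.2, so 76 per arm, and 76/0.9 rounds up to 85. The unequal-variance t-test gives 77 per arm, and 77/0.9 = 85.6 rounds up to 86, as stated. The evaluable number used below is 77 per arm.

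**Step 2: the two tests.** Chi-square is X² = Σ(O − E)²/E over a 2 × 4 table, with (2 − 1)(4 − 1) = 3 degrees of freedom. The sum does not depend on the order of the columns. The Mann–Whitney test gives each grade its mid-rank and compares the rank sums with a tie-corrected variance. It has one degree of freedom and a direction.

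**Step 3: simulated power.** Changes were cut at 25%, 50% and 100% of the baseline diameter (for 6 mm: 1.5, 3 and 6 mm), and empty grades were dropped. Half the planned effect is 0.92/2 = 0.46 mm. The common standard deviation of 1.74 is √((2.12² + 1.25²)/2). Entries are power by chi-square / power by rank test on the grades.

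| Scenario | 5 mm | 6 mm | 8 mm | Gain in points |
|---|---|---|---|---|
| Half effect, common SD 1.7 | 17% / 26% | 18% / 24% | 13% / 20% | 6 to 9 |
| Full 0.92 mm, common SD 1.74 | 62% / 76% | 61% / 72% | 55% / 66% | 11 to 15 over repeat runs |
| Half effect, pilot SDs 2.12 and 1.25 | 84% / 85% | 87% / 87% | 86% / 90% | 0 to 5 over repeat runs |
| Full pilot means and SDs | 97.9% / 98.3% | 98.8% / 98.9% | 99.0% / 99.4% | 0.1 to 0.4 |

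Two variants test the low end. With changes rounded to whole millimetres, the third row becomes 82% / 88%, 82% / 87% and 76% / 84%, a gain of 5 to 8 points. At the full pilot effect, with whole-millimetre diameters and baselines that vary around assumed means of 6, 8 and 10 mm, the figures are 96.7% / 98.0%, 94.4% / 97.7% and 93.8% / 97.5%, a gain of about 1 to 4 points.

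The gain is small with unequal standard deviations because the wider spread in the CJG arm itself separates the grade distributions, and chi-square detects that too.

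**Step 4: type I error.** With identical grade distributions in both arms (three assumed distributions), chi-square rejected in 2.8% to 5.0% of runs and the rank test in 4.6% to 5.0%.

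**The case against.** The strongest reply is that no sentence assigns a test to the response grades. The rule is a general one in a condensed article, and an analysis plan might name an ordinal test or merge the grades into responders and non-responders. The Introduction reports the preliminary study as a single effective rate (52.2%), and for a two-by-two table chi-square is appropriate. This stands in part. The article does not say that the grades will be merged here, and they are categorical under a rule that names a test. The objection is to that stated rule, and it would fall away if the grades were merged.

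A second reply also has force. The same information is analysed with its order intact through the continuous reduction rate and the mixed model for diameter change. In the half-effect scenario with a common standard deviation of 1.7 mm, Mann–Whitney on the ungraded change has 36% to 37% power, more than either test on the grades. This limits the point to a refinement.

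A reader might infer more than the documents support:

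- That the grades are a key secondary outcome. The protocol never ranks them so; they classify the reduction rate.
- That the anxiety and depression bands are affected too. BAI and BDI-II are scores, which the rule for continuous variables covers, and nothing says that the bands are tested.
- That the adherence groups need a rank test. Section 2.7.2.1 promises only counts and percentages, and intake above 120% of the prescribed amount is not better adherence than 80–120%.
- That a significant chi-square result could not be interpreted. The direction can be read from the reported proportions; the test simply does not target it.

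**Conclusion.** The point holds as a minor improvement, limited to the four response grades. The stated rule is order-blind for an outcome that is ordered by construction. How much power this costs depends on the standard deviations as well as on the effect size. The loss is roughly 6 to 15 points if the arms share a common standard deviation, and about 0 to 5 points if the pilot's unequal values hold (up to 8 in the variant with whole-millimetre rounding). It would therefore be wrong to say that the loss appears only when the effect is smaller than planned, or that it is always large. All these figures rest on assumed baseline diameters and normal changes. There is no excess of false positives, the stated sample size reproduces, and the primary conclusion does not change.

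**What to change.** Add one sentence to section 2.14: the grades from complete response to progressive disease will be compared between arms at 3 months and at 1 year by the Mann–Whitney test, with the count and percentage in each grade reported. A proportional-odds model giving a common odds ratio with its 95% confidence interval is an alternative that also yields an effect size. Keep chi-square or Fisher's exact test for unordered variables such as sex. If the grades are in fact to be merged into responders and non-responders, state that and define the cut; chi-square then suffices. Make the choice before unblinding, so that it cannot look driven by the results. Both methods are available in SPSS, the software already named, and no extra data, visits or patients are needed.

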## Discussion

3

Serial CT surveillance continues to be the primary strategy for managing pGGNs. However, extended monitoring can lead to considerable psychological distress in patients due to the perceived risk of malignant transformation, and premature surgical intervention may result in unnecessary compromise of pulmonary function. This dual challenge underscores the need for safe and effective complementary therapeutic strategies. Notably, existing clinical studies focus on refining radiological interpretation or identifying biomarkers for early prediction of malignant transformation, and no pharmacotherapeutic options are currently recommended for stable pGGNs. A recent phase II trial investigating programmed death-1(PD-1) inhibitors for these nodules reported an objective response rate of only 13.9%, which falls short of the efficacy threshold required for clinical application (24).

As an adjunct to conventional medical treatments, TCM exhibits considerable potential in influencing the progression of pulmonary nodules. Empirical evidence suggests that TCM can effectively reduce both the diameter and quantity of nodules, increase nodule density, and enhance patient immunity through mechanisms characterized by multi-target and multi-system effects. A network pharmacology study focusing on TCM formulations for ground-glass nodules revealed that herbal preparations containing quercetin represent promising therapeutic candidates. Their bioactivity involves modulation of hypoxia inducible factor-1(HIF-1) and mitogen-activated protein kinase (MAPK) signaling pathways, influencing tumor cell proliferation, transendothelial neutrophil migration, invasive capacity, and chemoresistance (25). Most of herbs in CJG contain quercetin, including *V. segetalis, P. grandiflorus, A. bidentata, C. aurantium,* and *T. kirilowii* (26–28). Additionally, *curcumin*, derived from *C. longa*, demonstrates significant anti-inflammatory and antioxidant properties, inhibiting the viability and proliferation of lung cancer cells through the induction of autophagy, promotion of apoptosis, and arrest of the cell cycle (29). And the mineral compound *Pumex*, which is enriched with trace elements such as calcium, magnesium, and strontium, contributes to the resolution of nodules by modulating ion channels, activating cytokines, and reprogramming metabolic pathways.

The direct cellular impacts of the human microbiota and microbial metabolites have the potential to reprogram the pulmonary microenvironment, thereby facilitating early-stage lung cancer. Current research suggests that the lung microbiome *Faecalibacterium* and *Blauti*a may exert protective effects against the progression of early lung cancer from ground-glass nodules to solid nodules, whereas *Ralstonia* may contribute to malignant transformation (30). The metabolites of these microbes are primarily involved in energy metabolism pathways. Additionally, the microbiota plays a crucial role in the translation of TCM. TCM extracts, monomers, and compound formulations can exhibit antitumor effects by modulating the composition of the gut microbiota and endogenous metabolites, restoring the integrity of the intestinal barrier, and regulating immune and metabolic processes (31). Our team developed a lung nodule risk prediction system using 16S rRNA sequencing and machine learning, which identified distinct salivary microbiota profiles between persistent nodules and healthy controls, as well as between benign and malignant nodules (32, 33). Besides, our up-front clinical trial on gut microbiota during CJG intervention for ground-glass nodules in the lung showed that this formulation altered gut microbiota, notably increasing *Weissella* abundance, which may influence clinical outcomes (34). However, this study specifically includes ground-glass nodules patients combined with constipation. And the small sample size, short duration, and unstable microbial findings limited deeper exploration of the interactions between CJG, gut microbiota, and ground-glass nodules. Thus, we hypothesize that CJG may affect pGGNs by altering the oral and gut microbiota’s composition and metabolic pathways. Our integrated multi-omics approach (16S rRNA sequencing and GC–MS metabolomics) serves as a powerful *in vivo* “wet lab” experiment conducted directly on patient-derived biospecimens. By analyzing the salivary and gut microbiota alongside their metabolic profiles, we aim to move beyond correlation and infer potential causal biological pathways through which CJG may exert its effects. Subsequent KEGG pathway enrichment analysis of identified differential metabolites will specifically highlight altered host or microbial metabolic pathways (e.g., involving inflammation, oxidative stress, or cellular proliferation), effectively bridging the gap between CT imaging findings and underlying molecular mechanisms. This bioinformatic exploration provides a robust hypothesis-generating framework for future targeted *in vitro* or *in vivo* mechanistic studies on specific signaling pathways.

This triple-blind, multicenter, randomized, placebo-controlled trial is crucial for exploring TCM as a complementary treatment for pGGNs. Beyond the primary radiological endpoint, the study also assesses secondary outcomes, including anxiety (measured by BAI), depression (assessed using BDI-II), and quality of life (evaluated through SF-36), to comprehensively capture the holistic benefits of TCM. Additionally, the trial explores potential mechanisms underlying these effects through 16S rRNA gene sequencing and metabolomic analysis of saliva and stool samples. These extensive assessments are underpinned by the study’s rigorous methodology, which incorporates randomization to mitigate confounding factors, stringent triple-blinding to reduce bias, and a multicenter design to enhance the reliability and generalizability of the findings. While the Traditional Chinese Medicine (TCM) intervention is confined to a duration of 3 months—selected based on preliminary data and practical considerations—participants’ nodule status is monitored for more than a year to assess potential long-term effects. However, this short intervention may not fully capture TCM’s benefits, which usually appear over longer periods. Future research should explore extended treatment durations to better evaluate lasting effects. Other limitations include reliance on CT scanner performance, resolution, and subjective interpretations by radiologists, which may lead to variability in feature descriptions and reporting standards. Additionally, this study was conducted in Sichuan Province, China, and while the sample size was adequate for primary outcomes, it may not represent global genetic, lifestyle, and environmental diversity. TCM practices can vary by region, and although CJG is standardized, its effects might be influenced by local diets or constitutions. Thus, our findings may not be generalizable to other populations. Future multicenter trials with diverse ethnic and geographical backgrounds are needed to validate the universal applicability of CJG.
